# The study evaluating the effect of probiotic supplementation on the mental status, inflammation, and intestinal barrier in major depressive disorder patients using gluten-free or gluten-containing diet (SANGUT study): a 12-week, randomized, double-blind, and placebo-controlled clinical study protocol

**DOI:** 10.1186/s12937-019-0475-x

**Published:** 2019-08-31

**Keywords:** Depression, Probiotics, Gluten-free diet, Inflammation, Intervention study, Gut-brain axis, Gut permeability, Gut microbiota, EEG functional connectivity, Study protocol

## Abstract

**Background:**

Current treatment of major depressive disorder (MDD) often does not achieve full remission of symptoms. Therefore, new forms of treatment and/or adjunct therapy are needed. Evidence has confirmed the modulation of the gut–brain–microbiota axis as a promising approach in MDD patients. The overall purpose of the SANGUT study—a 12-week, randomized, double-blind, and placebo-controlled Study Evaluating the Effect of Probiotic Supplementation on the Mental Status, Inflammation, and Intestinal Barrier in Major Depressive Disorder Patients Using Gluten-free or Gluten-containing Diet — is to determine the effect of interventions focused on the gut-brain-microbiota axis in a group of MDD patients.

**Methods:**

A total of 120 outpatients will be equally allocated into one of four groups: (1) probiotic supplementation+gluten-free diet group (PRO-GFD), (2) placebo supplementation+ gluten-free diet group (PLA-GFD), (3) probiotic supplementation+ gluten containing diet group (PRO-GD), and (4) placebo supplementation+gluten containing diet group (PLA-GD). PRO groups will receive a mixture of psychobiotics (*Lactobacillus helveticus* R0052 and *Bifidobacterium longum* R0175), and GFD groups will follow a gluten-free diet. The intervention will last 12 weeks. The primary outcome measure is change in wellbeing, whereas the secondary outcome measures include physiological parameters.

**Discussion:**

Microbiota and its metabolites have the potential to influence CNS function. Probiotics may restore the eubiosis within the gut while a gluten-free diet, via changes in the microbiota profile and modulation of intestinal permeability, may alter the activity of microbiota-gut-brain axis previously found to be associated with the pathophysiology of depression. It is also noteworthy that microbiota being able to digest gluten may play a role in formation of peptides with different immunogenic capacities. Thus, the combination of a gluten-free diet and probiotic supplementation may inhibit the immune-inflammatory cascade in MDD course and improve both psychiatric and gut barrier-associated traits.

**Trial registration:**

NCT03877393.

## Background

Major depressive disorder (MDD) is a leading cause of disability around the world [1]. In European countries, the cost of mood disorders is estimated to be about €170 billion per year [2]. This is alarming, as more than 350 million people worldwide live with depression; worse yet, about 50% of major depressive disorder patients remain untreated [2]. A diagnosis based on the symptomatology, a lack of biological markers, failure to achieve full remission, and high percentage of suicidal patients make MDD a challenge in the twenty-first century. A high recurrence rate and a large number of non-responders justify the urgent need to look for new therapeutic approaches [3]. Traditionally considered a brain-based disease, MDD is increasingly being recognized as a systemic whole-body illness [4]. The evidence for reduction in peripheral inflammation as a promising methods for depression management is still growing [5–7].

The immune system has a powerful impact on brain function and activity [8, 9]. In 1991, Smith proposed the macrophage theory of depression, where immune and inflammatory imbalances are the main factors leading to the onset or maintenance of MDD [10]. The author suggested that the intestine is a potential immune activation gate. Bidirectional signaling via the immune, endocrine, neural, and metabolic pathways occurs between the gastrointestinal (GI) tract and brain [11]. In his earlier works, Smith termed this connection the “food-gut-allergy-behavior axis” [10]. The intestines, having one of the largest surface areas interacting with the external environment, are exposed to more antigens than any other part of the body [12]. One of the proposed causes leading to macrophage activation is an abnormal immune response to food compounds in mechanisms other than classic allergy (i.e. immunoglobulin-E (IgE)-mediated food allergy). The interplay between genetic and environmental factors may lead to the disruption of gut proteins such as tight junctions (TJs) and subsequently to the loss in epithelial wall integrity and both gut and blood-brain barrier (BBB) permeability [13]. Disruption of the intercellular TJs may be the initial phenomenon related to uncontrolled molecule translocation (i.e. toxins, antigens, and bacteria) into the blood, which promotes proinflammatory cytokine synthesis and pro/anti-inflammatory imbalance [14].

A growing amount of evidence indicates that microbiota eubiosis may be one of the potential factors supporting gut function and proper communication between the gut and the brain [15–17]. The gut microbiota performs essential functions influencing gut wall integrity (i.e. the upregulation of mucin genes, immunoglobulin A (sIgA), and cytokine secretion, suppression of intestinal inflammation, and restoration of TJs structure [18]. Gut dysbiosis affects alternations in intestinal permeability [19, 20]. Beyond the macrophage theory of depression, microbial dysbiosis is associated with impaired epithelial barrier, bacterial translocation, decreased regulatory T cells in the gut mucosa, and has been shown to promote inflammation [21]. A quantitative and qualitative recovery within the composition of microbiota could therefore have a beneficial effect on inflammation and the regulation of transport via the gut to blood circulation [22–24].

Two meta-analyses confirmed the beneficial effect of probiotics in MDD patients [25, 26]. However, the potential mechanisms of action are obscure. The proposed effect of probiotics on mental state involves not only an improvement in gut wall integrity and inflammation suppression (including the influence of bacteria-derived metabolites on the microenvironment) [27], but also regulation of the hypothalamic-pituitary-adrenal (HPA) axis, thereby affecting the response to stress modulation [28]. Neural activation of stress circuits by microbiota could directly affect central nervous system (CNS) functioning. Activation of the HPA axis and excessive cortisol secretion are potential factors leading to disruption of gut wall integrity, macrophage activation, and the secretion of proinflammatory molecules, consequently maintaining the abnormality [15, 29].

Other potential factors interacting with the gut mucosa layer are food-derived compounds, especially gluten, a complex with high immunogenic properties consisting of albumins, globulins, glutenins, and gliadins [30, 31]. Gluten proteins have been found to regulate zonulin, occludin, and claudin, all previously reported to influence intestinal permeability for macromolecules [32, 33]. Gluten is hydrolyzed by gastrointestinal proteases; however, an abundance of proline and glutamine leads to incomplete gluten degradation [34]. Gluten peptides and other food-derived compounds can be absorbed and transported into the organs by blood circulation, and could provoke an immune-inflammatory cascade [14]. In individuals with gluten-related disorders, a gluten-free diet has high potential to decrease the severity of depression symptoms [35]. However, the results of studies examining the prevalence of the abnormal response of MDD patients to food compounds are contradictory [14, 36]. Gluten restriction could lead to a significantly lower intake of whole grains [37]. Reduced consumption of cereal products may be linked with a higher risk of heart diseases. Moreover, carbohydrates derived from wheat have been shown to stimulate the activity of Bifidobacteria in the colon and their elimination could negatively impact gut bacteria specificity [38]. To sum up, a gluten-free diet is not simply either ‘pro-‘ or anti-inflammatory’ and an immune response to potential food triggers depends on individual variability [39].

The formulation with potential beneficial psychological effects is a mixture of two psychobiotic (probiotic with mental health benefits) [40]) strains: *Lactobacillus helveticus* R0052 and *Bifidobacterium longum* R0175. A study with healthy volunteers showed that supplementation with mixture of *L. helveticus* R0052 and *B. longum* R0175 decreased anxiety and depression symptoms [41]. However, no study has examined the effect of this psychobiotic mixture on both mental and somatic health in patients suffering from MDD. As a result, there is an urgent need to determine the utility and differences in the effectiveness of a gluten-free diet and probiotic supplementation, together and separately, in the management of depression.

## Methods/design

### Aim and hypothesis

The main goal of the SANGUT study (a 12-week, randomized, double-blind, and placebo-controlled study) is to determine the effect of probiotic supplementation, a gluten-free diet, and their combination on the mental state, inflammatory markers, and gut permeability markers in adult patients with MDD. The primary hypothesis is that probiotic supplementation and/or a gluten-free diet will reduce the symptoms of depression, decrease levels of inflammatory markers, and favorably affect the integrity of the intestinal mucosal barrier.

### Study design

The trial will be a prospective, randomized, double-blind (placebo = probiotic) controlled design that will last 12 weeks. The trial was registered in the clinicaltrials.gov registry (ClinicalTrials.gov identifier: NCT03877393).

### Study population

A total of 120 adult volunteers with a diagnosis of major depressive disorder (MDD) will be recruited for this study. To be eligible in the trial, subjects must fulfil all of the inclusion criteria and none of the exclusion criteria, as stated below. The following inclusion criteria will be adopted:
Outpatients aged 18–60 years,Written informed consent to participate in this study before any study-mandated procedure,Meet the DSM-5 criteria for major depressive disorder (MDD) [42],Body mass index (BMI) ≥18.5 kg/m^2^ and ≤ 30 kg/m^2^,MADRS (Montgomery-Asberg Depression Scale) total score of 20 points or more (moderate or severe depression) at screening (V0) and at baseline (V1), andA willingness and motivation to follow the study protocol.

The exclusion criteria will be as follows:
Diagnosis of autoimmune, neurological, immunocompromised, thyroid, inflammatory bowel diseases, irritable bowel syndrome, diabetes, cancer, and/or IgE-dependent allergy;Psychiatric comorbidities (except specific personality disorder) including mental retardation, organic brain dysfunction, or addiction (except nicotine and caffeine);High risk of suicide in the investigator’s opinion;An infection one month before the study baseline visit (V1);The use of antibiotics and/or probiotics three months prior to the study;Glucocorticosteroids and/or metformin treatment;Dietary supplementation (except for vitamin D according to the “Vitamin D supplementation guidelines, 2018” [43]);Changes in a pharmacotherapy and/or psychotherapy of MDD 2 weeks before the trial entry;No specific (e.g. elimination, vegan, reduction) diet and changes in physical activity 4 weeks before the trial entry, andPregnancy or lactation.

Reasons for the participant to be discontinued from the study:
Withdrawal of informed consent,Lack or incomplete compliance with the diet and/or probiotic supplementation,Non-attendance at the study visits,Exclusion criteria found after enrollment, andAny serious adverse event during the intervention period (based on data safety monitoring).

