### Dietary interventions

#### Probiotic supplementation

The probiotic groups (PRO-GFD and PRO-GD) will receive one capsule containing the probiotic mixture powder (Sanprobi Stress; Sanprobi sp. z o.o., sp.k., Szczecin, Poland) in the amount of 3 × 10^9^ colony forming units (CFU) per day divided into two equal doses. The probiotic preparation will contain two bacteria strains: *Lactobacillus helveticus* Rosell®-52, *Bifidobacterium longum* Rosell®-175 and excipients: potato starch, magnesium stearate, and the capsule shell of hydroxypropyl methylcellulose. The placebo groups (PLA-GFD and PLA-GD) will receive the same capsule containing only the excipients, i.e. maize starch, maltodextrins, and the capsule shell. The placebo will be indistinguishable in color, smell, and taste from the probiotic formulation. Participants will be asked to consume the supplements before breakfast. Each of the study participants will be asked to collect the blister packs to evaluate compliance after the study.

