#### Elimination diet

The patients in the GFD groups will follow the elimination diet containing no gluten. During the Baseline Visit (V1), participants will be educated about the rules of gluten-free diet restrictions and informed that the elimination diet is not a caloric restriction diet so the consumption of nutrients should not be changed. Information on the origins of gluten, the grains containing gluten, and highly processed food with gluten, will be received by all participants. They will be encouraged to consume natural, fresh foods and read the labels of food products in order to evaluate the gluten content. To avoid potential outcome bias resulting from a balanced diet and change in dietary habits, participants will be asked to follow their usual eating patterns, excluding gluten-containing products.

Before the intervention is implemented (between V0 and V1), patients will be asked to keep a diet diary (a 3-day food record). Changes and modifications in typical food consumption (based on the 3-day food record) during the consultation (at baseline, V1) will be proposed by a dietitian. Moreover, each participant will receive a list of products to be eliminated as well as a list of substitutes with the same taste, organoleptic properties, and nutritional values. A guide on the gluten-free diet and seven proposed menus for breakfast, lunch, dinner, and snacks will be given to each participant. The diet protocol will include only qualitative data, without the portion sizes, to keep the amount of food consumed at the current level. Patients will be educated about sticking to a diet by a dietitian during a consultation (visit V1).

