### Methods of assessment

#### Dietary assessment and diet adherence

Diet assessment and adherence to the protocol will be examined using the Food Frequency Questionnaire with six answers (FFQ-6) validated on a Polish population [45]. The FFQ questionnaire will be used to assess intake of 62 products (including the main gluten sources) divided into eight groups that are consumed in Poland. Respondents will have to select one out of six frequency categories: (1) never or almost never, (2) once a month or more rarely, (3) several times a month, (4) several times a week, (5) daily, and (6) several times a day. The FFQ questionnaire will be filled out by a clinical dietitian with experience in conducting nutritional interviews. Using the “Album of photographs of food products and dishes” [54], participants will determine the serving sizes of the consumed products. The amount of food intake which is not included in the aforementioned album will be determined using the ilewazy.pl website [55]. Patients will also be asked to complete a 3-day food record (including two weekdays and one weekend day) before the Baseline Visit (V1), and twice in the study period (first between 1 and 6 weeks from the implementation of the diet, and for the second time between 6 and 12 weeks from the implementation). Based on the food records, we will be able to estimate the nutritional value and assess the intake and percentage of consumed nutrients from the recommended amounts. According to the method from earlier studies (multiplying protein contained in gluten cereal by 0.8) [56, 57], gluten in patients’ diet will be estimated from the FFQ questionnaire and 3-day food records. Based on the FFQ results, alcohol consumption will also be estimated. A possible influence of other nutritional factors (energy value, nutrient intake) on the obtained results will be checked before and during the intervention based on dietary diaries.

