### Data management and analysis plan

#### Data analysis principles

To evaluate the efficacy of the intervention on the well-being of patients, the following changes from the baseline (V1) to the end of the study (V3) will be determined as primary outcomes:
The severity of depression symptoms:
MADRS total scoreBDI total scoreThe severity of psychopathological impairment:
SCL-90 total scoreThe quality of life:
SF-36 total scoreStress levels:
PSS-10 total score

To evaluate the effect of the intervention on physiological parameters [79], the following changes will be determined as secondary outcomes:
In serum, from the screening (V0) to the end of the study (V3), levels of:
proinflammatory biomarkers: hs-CRP, Il-6, Il-1beta, and TNF-alphagluten sensitivity biomarkers: anti-TG2 IgG antibodies and anti-AGA IgG/IgA antibodiesintestinal permeability biomarkers: I-FABP/FABP-2 and LBPmetabolism biomarkers: total cholesterol, LDL cholesterol, HDL cholesterol, TG, glucose, and insulinHPA axis biomarker: cortisolliver function biomarkers: ALT and ASTIn stool, from the baseline (V1) to the end of the study (V3):
taxonomic and functional analysis of gut bacterial communitySCFAs levelsBrain activity, from the baseline (V1) to the end of the study (V3):
EEG analysisGastrointestinal symptoms, from the baseline (V1) to the end of the study (V3):
GSRS scale.

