To the best of our knowledge, this will be the first intervention study assessing the efficacy of both probiotic supplementation and a gluten-free diet and comparing the effect of both interventions and their combination in MDD patients. The protocol and the outline were developed by a multidisciplinary researcher team. The methodology employed in the study benefited greatly from our diverse set of knowledge, experience and perspectives. Considering the highly rigoristic selection criteria, the participant group is relatively large. Rigorous procedures established for this trial will be followed by well-trained researchers to ensure that research will be conducted in accordance with standards of best practice. The measurements listed above will be introduced to reduce the potential bias related to confounding variables (e.g. smoking, physical activity, and diet).

There may be some possible limitations in the design of the study:

First, the impossibility of blinding the diet is a factor that could affect assessment of both the participant and investigator. For this reason, the researcher evaluating the severity of symptoms will not be informed as to whether the patient will be allocated to the GFD or GD arm of intervention.

Second, the lack of motivation is a symptom commonly experienced by MDD patients and could contribute to the non-attendance at the study visits, incomplete implementation of the intervention, or failure to complete the intervention.

Third, patients in the GFD groups receiving dietary advice might try to introduce other changes in food consumption (e.g. reduce the food portion size and/or consume more vegetables and fruits). Therefore, health improvement may not be specific to the implemented gluten-free diet.

Finally, recall bias in self-reporting is another potential confounder of the study. However, dietary consultation and food intake assessment during the study period should minimize the likelihood of its occurrence.

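### Ending study participation for incomplete compliance or non-attendance risks selective loss of week-12 outcomes, plausibly more in the gluten-free arms, and can bias the diet comparison

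*Protocol article*

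**What the plan says.** The protocol article, Study population, introduces a list with "Reasons for the participant to be discontinued from the study". Two of its entries matter here: "Lack or incomplete compliance with the diet and/or probiotic supplementation" and non-attendance at study visits. The wording concerns the study as a whole, and the article mentions no outcome assessment after such a discontinuation.

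Other sections bear on how the rule would work:

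- Data analysis principles: "changes from the baseline (V1) to the end of the study (V3) will be determined as primary outcomes". A patient who leaves before V3 has no primary outcome.
- Elimination diet: "The patients in the GFD groups will follow the elimination diet containing no gluten". No elimination rule is described for the gluten-containing (GD) groups.
- Dietary assessment and diet adherence: adherence is followed with a food frequency questionnaire and with food records in both halves of the 12 weeks, so lapses can come to light before V3.
- Probiotic supplementation: "Each of the study participants will be asked to collect the blister packs to evaluate compliance after the study". This check covers all four arms.
- Discussion, limitations: "the lack of motivation is a symptom commonly experienced by MDD patients", with the remark that it could contribute to missed visits and incomplete implementation.
- Sample size calculation: about 81% power with 116 patients. The planned total is 120, in four arms of 30.

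**The concern.** Compliance is observed after randomisation and can depend both on the assigned arm and on the patient's condition. If it decides who is still measured at week 12, the patients with a primary outcome need no longer be comparable across arms. Two features make this more than a theoretical worry. The diet part of the rule asks much more of the GFD arms than of the GD arms, and the article itself ties poor implementation to a depressive symptom, while depression severity is among the primary outcomes.

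The diet effect is part of the primary hypothesis. Because this is a rule of conduct, the damage is done when the visit is not held: no later analysis plan can recover a V3 assessment that was never made.

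**Working it through.** **1. Can the rule remove primary outcomes unequally?** Set side by side, the sections give four links. Discontinuation is from the study. The primary outcome requires V3. Diet adherence is examined before V3. Only the GFD arms (2 × 30 = 60 of 120) have an elimination rule to break. The Discussion adds a possible link between non-compliance and illness. Selective and unequal loss is therefore a sound inference from the design, but not a documented fact.

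**2. The plan's own figure.** The article states 81% power at N = 116 without giving alpha, a numerical effect size, the number of measurements or their correlation. I assumed f = 0.25 (medium), alpha = 0.05, m = 4 measurements and correlation 0.5. For the between-group effect in a repeated-measures ANOVA:

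λ = N f² m / (1 + (m − 1) × 0.5) = 116 × 0.0625 × 4 / 2.5 = 11.6, with 3 and 112 degrees of freedom.

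Power is 0.812, so the figure reproduces, but only with inputs that the article does not state. With m = 3 it would be 0.783.

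**3. Room for loss.** (120 − 116) / 120 = 4 / 120 = 3.3%. Under the assumptions of step 2:

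| Loss | Patients left | Power |
|---|---|---|
| 5% | 114 | 0.804 |
| 10% | 108 | 0.779 |
| 15% | 102 | 0.752 |
| 20% | 96 | 0.722 |

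**4. Illustration of bias, with no true diet effect.** If a share p of an arm is non-compliant and improves less than the compliers by δ, the full-arm mean lies p × δ below the compliers' mean. Removing those patients raises the arm's mean by p × δ, so

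bias = (p in GFD − p in GD) × δ.

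With assumed losses of 25% and 10%:

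- δ = 0.5 SD: 0.15 × 0.5 = 0.075 SD
- δ = 1.0 SD: 0.15 × 1.0 = 0.15 SD

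That is 15% to 30% of an assumed 0.5 SD effect, in favour of GFD. In this scenario 60 × 0.75 = 45 and 60 × 0.90 = 54 patients remain, 99 in all. The standard error of the diet contrast is √(1/45 + 1/54) = 0.20 SD.

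**5. A second model.** Let compliance correlate r with improvement, and remove the least compliant share d of each diet group. The retained mean shifts by r φ(z_d) / (1 − d) SD, and the bias is the GFD shift minus the GD shift. The type I error is for a two-sided 5% test of the diet contrast, starting from 60 per diet.

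| Loss GFD / GD | r | Bias (SD) | Type I error |
|---|---|---|---|
| 20% / 5% | 0.2 | 0.05 | 0.057 |
| 20% / 5% | 0.3 | 0.07 | 0.066 |
| 20% / 5% | 0.5 | 0.12 | 0.094 |
| 30% / 5% | 0.2 | 0.08 | 0.067 |
| 30% / 5% | 0.3 | 0.12 | 0.088 |
| 30% / 5% | 0.5 | 0.19 | 0.159 |
| 20% / 20% | any | 0 | 0.050 |
| any | 0 | 0 | 0.050 |

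The smallest non-zero case examined (10% against 3.3%, r = 0.2) gives 0.02 SD. Every loss rate, δ and r in steps 4 and 5 is an assumption.

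**The case against.** The strongest reply is that the text says less than a critical reader might infer. Several stronger readings are tempting, and the document does not support them.

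- *The blister-pack count after the study removes outcomes.* It covers all four arms and comes when V3 should already have been measured. By itself it loses no outcome and creates no imbalance between diets. It would matter only if patients were then left out of the analysis.
- *The trial becomes a comparison of compliers.* The discontinuation list does not define an analysis set. The Statistical analysis section cites ICH E9 and names no per-protocol or completer population. Analysis sets may be fixed in a plan that is not shown.
- *Any lapse, or one missed visit, triggers removal.* The article gives no threshold, but a condensed article may leave that to the full protocol.
- *Losses will fall mainly in the GFD arms and will flatter the diet.* The capsule and attendance criteria apply to every arm. The Discussion says only that low motivation could contribute, not that non-compliers improve less. Entry also requires willingness and motivation to follow the protocol, which mitigates part of the risk. Lapses for practical reasons might carry no prognostic information.

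It is also fair to say that the illustrated bias in step 4 is below one standard error (0.075 / 0.20 and 0.15 / 0.20), and that any dropout, not only this rule, uses up the four-patient margin.

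All of this limits how firmly the point can be put. It does not remove it: the rule as written ends participation in the study, and neither the E9 citation nor a later analysis plan supplies outcomes that were not collected.

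**Conclusion.** The concern holds as a risk. Following the rule can lose week-12 outcomes selectively, plausibly more in the GFD arms, and can bias the diet comparison. Size and direction cannot be known from the article. Across the assumed scenarios the bias runs from about 0.02 to 0.19 SD in favour of GFD, with 0.075 to 0.15 SD for the simple case of 25% against 10% loss. It is zero if loss is equal across diets or compliance is unrelated to outcome.

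The 3.3% margin for loss is simple arithmetic from the stated 120 and 116. The power figures beyond it rest on the assumed inputs that reproduce the stated 81%.

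**What to change.** Remove compliance and non-attendance from the reasons for ending study follow-up. Record both, and continue the scheduled V2 and V3 outcome assessments for the patients concerned unless they withdraw consent. State that the primary analysis compares patients as randomised. Use compliance from blister packs and food records only in a per-protocol sensitivity analysis labelled as such.

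Whether a patient stops the diet or the capsules is a separate clinical decision that this change leaves alone. The serious-adverse-event criterion also stays as it is.

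The cost is a change of protocol wording and the effort of bringing non-compliant patients to visits that are already scheduled. The price in interpretation is a somewhat diluted effect estimate, since patients who did not follow the intervention remain in their assigned arm.
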